#### 16.1.1. Discontinuation of Study Treatment after CR

Discontinuation of treatment may be considered for patients who have attained a confirmed CR that have been treated for at least 24 weeks with pembrolizumab and had

## PEACOCC

---

at least two treatments with pembrolizumab beyond the date when the initial CR was declared. Patients who then experience radiographic disease progression may be eligible for up to one year of additional treatment with pembrolizumab via the re-treatment period at the discretion of the investigator if no cancer treatment was administered since the last dose of pembrolizumab, the patient meets the safety parameters listed in the Inclusion/Exclusion criteria, and the trial is open. Patients will resume therapy at the same dose and schedule at the time of initial discontinuation. Additional details are provided in Section 9.3.3.

### 16.1.2. Treatment beyond Equivocal Progression

If unconfirmed progressive disease (PD; based on RECIST v1.1) occurs before completion of the 24-month treatment period, the patient may continue to be treated until one of the following criteria is met:

- Confirmation of PD: The assessment of unconfirmed PD by RECIST v1.1 (baseline PD assessment) will be confirmed by a repeat evaluation at the next tumour assessment time point, but no sooner than 4 weeks later. If this confirms unequivocal progressive disease the patient should discontinue trial treatment.
- Meets any of the investigational product discontinuation criteria (Section 16.1)
- Clinical symptoms or signs indicating clinically significant PD such as the benefit-risk ratio of continuing therapy is no longer justified.
- Decline in Eastern Cooperative Oncology Group (ECOG) performance status compared to baseline.
- Rapid PD or threat to vital organs/critical anatomical sites (eg, spinal cord compression) requiring urgent alternative medical intervention, and/or continuation of study therapy would prevent institution of such intervention.

### 16.2. Future Data Collection

If a patient explicitly states they do not wish to contribute further data to the trial their decision must be respected, with the exception of essential safety data, and recorded on the relevant eCRF (Change of Status). In this event data due up to the date of withdrawal must be submitted but no further data, other than essential safety data, sent to UCL CTC.

### 16.3. Losses to Follow-Up

If a patient moves from the area, every effort should be made for the patient to be followed up at another participating trial site and for this new site to take over the responsibility for the patient, or for follow-up via GP. Details of participating trial sites can be obtained from the UCL CTC trial team, who must be informed of the transfer of care and follow up arrangements. If it is not possible to transfer to a participating site, the registering site remains responsible for submission of forms.

If a patient is lost to follow-up at a site every effort should be made to contact the patient's GP to obtain information on the patient's status.

## **17. TRIAL CLOSURE**

### **17.1. End of Trial**

For regulatory purposes the end of the trial will be when the last patient alive who has completed initial and re-treatment (if applicable) has two follow-up/survival follow-up assessments (either prior to or after progression) or dies, whichever occurs first and once all protocol planned exploratory research has been completed. At which point the 'declaration of end of trial' form will be submitted to the MHRA and Ethics Committee, as required.

Following this, UCL CTC will advise sites on the procedure for closing the trial at the site.

Once the end of trial has been declared, no more prospective patient data will be collected but sites must co-operate with any data queries regarding existing data to allow for analysis and publication of results.

### **17.2. Archiving of Trial Documentation**

At the end of the trial, UCL CTC will archive securely all centrally held trial related documentation for a minimum of 25 years. Arrangements for confidential destruction will then be made. It is the responsibility of PIs to ensure data and all essential documents relating to the trial held at site are retained securely for a minimum of 25 years after the end of the trial, and in accordance with national legislation.

Essential documents are those which enable both the conduct of the trial and the quality of the data produced to be evaluated and show whether the site complied with the principles of GCP and all applicable regulatory requirements.

UCL CTC will notify sites when trial documentation held at sites may be archived. All archived documents must continue to be available for inspection by appropriate authorities upon request.

### **17.3. Early Discontinuation of Trial**

The trial may be stopped before completion as an Urgent Safety Measure on the recommendation of the TSC or IDMC (see section 15.5.2 Trial Steering Committee (TSC) and 15.5.3 Independent Data Monitoring Committee (IDMC)). Sites will be informed in writing by UCL CTC of reasons for early closure and the actions to be taken with regards the treatment and follow up of patients.

### **17.4. Withdrawal from Trial Participation by a Site**

Should a site choose to close to recruitment the PI must inform UCL CTC in writing. Follow up as per protocol must continue for any patients recruited into the trial at that site and other responsibilities continue as per the Site Agreement.

## **18. STATISTICS**

### **18.1. Sample Size Calculation**

Assuming that the proportion of progression-free patients at 12 weeks will be 33%, a proportion <15% would be of no further interest [16]. Using A'hern's single-stage phase II design with 90% power and one-sided 5% significance level, a sample size of 48 patients is required with  $\geq 12$  patients alive and progression-free at 12 weeks to warrant further investigation. The sample size was calculated using "Sample size tables for clinical studies" software.

### **18.2. Statistical analysis**

#### **18.2.1. Analysis of main endpoint**

The number and percentage of progression-free patients at 12 weeks will be presented, with 90% two-sided confidence intervals for the percentage.

The proportion of progression-free patients is defined as the number of patients alive with complete or partial response or stable disease maintained at 12 weeks (as assessed by the site radiologist and/or investigator, using RECIST v1.1) divided by the number of patients in the analysis population. Only patients with tumour assessment at or beyond 12 weeks will be considered progression-free.

All eligible patients who received at least one cycle of pembrolizumab will be included in the analysis population (i.e. safety population).

Any patient found to be ineligible will be excluded and replaced.

#### **18.2.2. Analysis of secondary endpoints and secondary analyses**

##### **18.2.2.1. Progression-free survival**

Progression-free survival is defined as the time from start of treatment to progression or death from any cause (whichever comes first). All deaths will be included, whether they occur on study or following treatment discontinuation. For patients who have not died or progressed, progression-free survival will be censored at the date of last contact.

Kaplan-Meier survival methods will be used.

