### 10.3. Tumour Imaging and assessment of disease

#### 10.3.1. Evaluation of Efficacy

Tumour assessments will be based on RECIST v1.1 and will be performed according to the schedule presented in Appendix 1. Tumour assessments will be performed at baseline, after cycle 2 (6 weeks on treatment) and after cycle 4 (12 weeks on treatment) and thereafter after every 4 cycles (12 weekly) until progression.

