### 10.6.1. Survival Follow-up

Once a patient experiences confirmed disease progression or starts a new anti-cancer therapy, the patient moves into the survival follow-up phase and should be contacted by telephone every 12 weeks to assess for survival status and any AEs that require reporting as per section 13.2, until death, withdrawal of consent, or the end of the study, whichever occurs first.

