## PEACOCOC

---

treatment discontinuation. For patients who have not died or progressed, second progression-free survival will be censored at the date of last contact.

Kaplan-Meier survival methods will be used.

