### **18.2.2.5. Duration of Response**

For patients with an objective response, duration of objective response (DoR) is defined as the time from initial complete or partial response to disease progression or death on study from any cause (defined as death within 110 days of the last study treatment), whichever occurs first.

For patients with disease control (objective response or stable disease maintained  $\geq 12$  weeks), duration of disease control (DoC) is defined as the time from start of treatment to disease progression or death on study from any cause (defined as death within 30 days of the last study treatment), whichever occurs first.

A subset analysis of DoR and DoC will be performed only in patients re-treated. This analysis will be performed once over the whole study period and once over the Re-treatment phase only.

Kaplan-Meier survival methods will be used, and patients will be censored at the date of last contact.

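### Scan-based secondary endpoints (PFS, second progression, DoR, DoC) are censored at last contact, so time without scans can count as progression-free and raise the curves

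*Protocol*

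**What the plan says.** Section 18.2.2.1 gives the endpoint: "Progression-free survival is defined as the time from start of treatment to progression or death from any cause (whichever comes first"). It adds that all deaths count, including those after treatment has stopped. Its censoring rule is: "For patients who have not died or progressed, progression-free survival will be censored at the date of last contact". Starting another anticancer therapy is neither an event nor a censoring point.

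Section 18.2.2.2 (time to second progression) repeats the rule: "second progression-free survival will be censored at the date of last contact". Section 18.2.2.5 does so for DoR and DoC: "patients will be censored at the date of last contact". In 18.2.2.5 a death counts only within 110 days (DoR) or 30 days (DoC) of the last study treatment.

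On imaging, section 10.3.1 schedules scans at baseline, week 6 and week 12, and "thereafter after every 4 cycles (12 weekly) until progression". Section 10.6.1 then says: "Once a patient experiences confirmed disease progression or starts a new anti-cancer therapy, the patient moves into the survival follow-up phase", and that such a patient "should be contacted by telephone every 12 weeks to assess for survival status" and reportable adverse events. The tumour imaging row of Appendix 1 has no mark in the survival follow-up column.

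Three other places read differently. Section 10.4.2.3 drops follow-up visits when a patient has both progressed and moved to other treatment. Section 10.6 asks for disease status until progression, death, end of study or re-treatment. Appendix 1 footnote j continues imaging until progression.

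**The concern.** Progression can be recorded only while scans are being done. If scans stop and telephone calls continue, last-contact censoring keeps the patient in the risk set, counted as progression-free, with no means of observing the event. For PFS and second progression, the patient leaves the risk set at the last call or at a later death, which becomes a late event. For DoR and DoC, a death outside the 110- or 30-day window is not an event, so the patient is censored at last contact as still in response or disease control.

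The route is realistic. Sections 16.1 and 16.1.2 let treatment stop for toxicity, clinical signs or ECOG decline without confirmed radiological progression, and another therapy may follow.

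The bias runs in one direction. With a single arm there is no control group against which it could cancel. Section 3.1.3.1.2 describes PFS as a reference standard for clinical benefit, and section 4.1.2 asks whether pembrolizumab prolongs it, so these curves will be read against outside results.

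**Working it through.** **1. The plan's own figure.** The protocol states no figure for the PFS curve. Its design figure (section 18.1: null 15%, target 33%, one-sided 5%, 90% power, n = 48, at least 12 successes) reproduces by exact binomial:
- P(X ≥ 12 | n = 48, p = 0.15) = 0.0478
- P(X ≥ 12 | n = 48, p = 0.33) = 0.911

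This point does not touch it.

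**2. Inputs for an illustration.**
- From the protocol: 33% progression-free at 12 weeks (18.1); scans at weeks 6 and 12, then every 12 weeks (10.3.1); imaging ends at new therapy (10.6.1 as written); censoring at last contact (18.2.2.1).
- Assumed: exponential time to progression; new therapy at a constant rate, independent of progression; data cut-off spread evenly over weeks 52 to 156; median survival after progression of 30 weeks, 52 weeks, or no deaths.
- Assumed probability s that new therapy precedes progression itself: 0, 5%, 10% or 20%.

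**3. Curve if scans continue.** λ = −ln(0.33)/12 = 0.0924 per week (median 7.5 weeks).
- 24-week PFS = 0.33² = 10.9%.
- At 52 weeks the last scan was at week 48, so the estimate is 0.33⁴ = 1.2%.

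**4. Written rule, no deaths (closed form).** The new-therapy rate is μ = λs/(1 − s). A progression between scans t(k−1) and t(k) is seen only if therapy has not started by t(k). Hence

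S(24) = 1 − Σ [e^(−λt(k−1)) − e^(−λt(k))] · e^(−μt(k)), over t(k) = 6, 12, 24.

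The bracketed terms are 0.4255, 0.2445 and 0.2211.

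| s | μ | e^(−μt) at 6, 12, 24 | sum seen by week 24 | S(24) |
|---|---|---|---|---|
| 5% | 0.00486 | 0.9712, 0.9433, 0.8899 | 0.4133 + 0.2306 + 0.1967 = 0.8406 | 15.9% |
| 10% | 0.01027 | 0.9403, 0.8841, 0.7816 | 0.4001 + 0.2161 + 0.1728 = 0.7890 | 21.1% |
| 20% | 0.02310 | 0.8706, 0.7579, 0.5745 | 0.3705 + 0.1853 + 0.1270 = 0.6828 | 31.7% |

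Summing the same terms over all scans, the share who leave imaging before progression is seen is 7%, 14% and 27%. That is about 3, 7 and 13 of 48 patients.

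**5. Written rule with deaths** (simulation, 200,000 patients per scenario; main figure for 52-week median survival after progression, range over the three survival assumptions):

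| Leave imaging early | 24-week PFS | 52-week PFS |
|---|---|---|
| 0% | 11% | 1.2% |
| 7% | 15% (15–16%) | 5% (4–8%) |
| 14% | 20% (19–21%) | 10% (7–15%) |
| 27% | 28% (26–32%) | 18% (13–28%) |

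The no-deaths end of each range agrees with step 4. Censoring at the last scan before new therapy gave about 11% and 1.2% in every row, matching the curve with full imaging. That agreement depends on switching being independent of progression.

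**6. What the illustration leaves out.** It omits the end-of-treatment scan in section 10.5, which applies to patients who stop for reasons other than progression unless they were imaged in the preceding 4 weeks. That scan would catch some progressions and reduce the bias. The illustration also does not measure the gap that remains if imaging does continue to progression.

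**The case against.** The strongest objection is to the premise. A reader might infer that imaging definitely stops at new therapy. The protocol does not support that as a settled fact: sections 10.4.2.3 and 10.6 and footnote j all point to imaging until progression, and only section 10.6.1 and the blank Appendix 1 cell say otherwise. This objection stands. If scans continue, what remains is the gap between last scan and last contact. In pre-progression follow-up that gap is small, because the 12-weekly visit includes the scan. It is wider on treatment, where visits are 3-weekly, and for patients who miss scans but can still be reached. The conflict does not make last contact the right date.

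A reader might also infer that the trial's go/no-go result is inflated. It is not: section 18.2.1 counts a patient as progression-free only with a tumour assessment at or beyond 12 weeks.

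A definite size is not supported either, since the switching rates have no source in the protocol. Nor is a slower progression rate a safe basis: a median PFS of 16 weeks would imply 0.5^(12/16) = 59% progression-free at 12 weeks, far from the planned 33%.

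Finally, compulsory censoring at new therapy is open to challenge. It would drop later deaths that section 18.2.2.1 includes, and it is informative if patients switch because they are deteriorating. That also stands, so it belongs in a sensitivity analysis. Last-scan censoring for patients without an event does not have the first of these problems.

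**Conclusion.** The point holds for the secondary time-to-event endpoints. The protocol itself fixes last-contact censoring for four endpoints that depend on scans, and one of its follow-up sections takes patients off imaging while contact continues. Followed as written, these rules bias PFS, second progression, DoR and DoC upwards.

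The size is unknown. Under the stated assumptions, 24-week PFS is overstated by about 4 to 17 percentage points when 7% to 27% of patients leave imaging early (52-week median survival after progression), and by nothing if no one does. It would be smaller if imaging continues to progression or if the end-of-treatment scan catches progressions.

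The primary endpoint, its decision rule and the sample size are unaffected. This should be fixed before analysis, but it does not threaten the trial's main conclusion.

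**What to change.** 1. In sections 18.2.2.1, 18.2.2.2 and 18.2.2.5, censor patients without progression or a counted death at the last evaluable tumour assessment (for PFS, at first dose if there is none). Keep last-contact censoring for overall survival only.
2. Reconcile section 10.6.1 and the Appendix 1 imaging row with sections 10.4.2.3 and 10.6 and footnote j, so that it is clear whether imaging continues after new therapy starts without progression.
3. State how new anticancer therapy before progression is handled, consistently with the inclusion of all deaths in section 18.2.2.1.
4. Show two sensitivity analyses: censoring at the last scan before new therapy, and the current last-contact rule.

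Cost: wording only for the analysis sections. Imaging and subsequent anticancer therapy are already recorded, and the analysis change needs no extra patients or visits. PFS, DoR and DoC figures may become slightly less favourable. Last-scan censoring may itself be informative if patients stop being scanned because they are deteriorating, which is why both sensitivity analyses should be reported.

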##### **18.2.2.2. Time to second disease progression (Re-treatment period)**

Time to second disease progression refers to progression in those patients re-treated on trial after their first progression. It is defined as the time from diagnosis of first progression during or after their initial pembrolizumab therapy to second progression or death from any cause (whichever comes first), during or after their retreatment pembrolizumab. All deaths will be included, whether they occur during the re-treatment period or following

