### 8.1.2.1 Re-treatment Pre-registration Assessments

The following assessments or procedures are required to evaluate the suitability of patients for re-treatment (see also Appendix 1 'Schedule of Procedures/Assessments'). All assessments must be completed within 28 days prior to the patient being re-registered (unless otherwise indicated).

- **Medical history.**
- **Full physical exam** including weight
- **Vital signs:** heart rate, respiratory rate, blood pressure, temperature and oxygen saturation (O2 sats).
- **Concomitant medication review.**
- **ECOG performance status.**
- **CT scan of chest, assessable by RECIST v1.1.**
- **CT scan or MRI scan(s) assessable by RECIST v1.1** of the pelvis, abdomen and brain.
- **Bloods:** Full blood count and liver function tests, urea & electrolytes, International Normalized Ratio (INR), thyroid function tests, serum calcium and urinalysis (within 10 days prior to registration).
- **HIV type 1/2, Hepatitis B and C testing.**

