### AND

- Experienced a confirmed radiographic disease progression according to RECIST v1.1 after stopping their initial treatment with pembrolizumab
- Did not receive any anti-cancer treatment since the last dose of pembrolizumab
- Has a performance status of 0 or 1 on the ECOG Performance Scale
- Demonstrates adequate organ function as detailed in Section 7.2.1.
- Female patient of childbearing potential should have a negative urine or serum pregnancy test within 72 hours prior to receiving retreatment with study medication.
- Female patient of childbearing potential should be willing to use a highly effective form of contraception as detailed in section 7.3.1.
- Does not have an ongoing history or current evidence of any condition, therapy, or laboratory abnormality that might interfere with the patient's participation for the re-treatment period and full duration of the trial or is not in the best interest of the patient to participate, in the opinion of the treating investigator.

Patients who restart treatment will be retreated at the same dose and dose interval as when they last received pembrolizumab.

Permanent discontinuation of re-treatment is required if any of the following occur:

- documented and confirmed disease progression by RECIST v1.1 criteria
- unacceptable adverse event(s)
- intercurrent illness that prevents further administration of treatment
- investigator's decision to withdraw the patient
- patient withdraws consent
- pregnancy of the patient
- non-compliance with trial treatment or procedure requirements.

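### Time to second progression runs from first progression but only in re-treated patients, so the wait before re-treatment is event-free by construction and lengthens the estimate

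*Protocol*

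**What the plan says.** Section 18.2.2.2 fixes each element of this endpoint.

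- **Analysis set:** "Time to second disease progression refers to progression in those patients re-treated on trial after their first progression".
- **Origin and event:** "the time from diagnosis of first progression during or after their initial pembrolizumab therapy to second progression or death from any cause".
- **When events count:** "during or after their retreatment pembrolizumab".
- **Censoring and estimator:** "second progression-free survival will be censored at the date of last contact", and "Kaplan-Meier survival methods will be used". The section mentions no landmark, no delayed entry and no later origin.

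Section 9.3.3 sets the entry conditions for re-treatment. One of them is: "Experienced a confirmed radiographic disease progression according to RECIST v1.1 after stopping their initial treatment with pembrolizumab". The others include ECOG 0 or 1, adequate organ function and no anti-cancer therapy since the last pembrolizumab dose. Sections 8.1.2 and 8.1.2.1 add consent, re-screening with new scans, and re-registration.

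**The concern.** Membership of the analysis set is decided after time zero. A patient who dies, becomes unfit or starts another therapy between first progression and the first re-treatment dose never enters the set. Those who do enter carry that interval as follow-up in which no event was possible. This is guaranteed, or immortal, time.

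If the result is read as how long re-treatment holds the disease, waiting time is credited to the second course. There is also a wording conflict: the definition covers a first progression that occurs while initial therapy is still being given, whereas section 9.3.3 opens re-treatment only to progression after stopping it.

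**Working it through.** **The plan's own figures.** The protocol gives no number for this endpoint. Its only design figure is the A'Hern rule in section 18.1 (48 patients, at least 12 progression-free, 15% against 33%). Exact binomial calculation reproduces it: one-sided error 0.0478, power 0.911, and 48 is the smallest sample size that meets the criteria. It does not bear on this point.

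**Direction, from the text alone.**

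1. A patient is analysed only if re-treated, hence alive at the first re-treatment dose. A death in the gap is impossible in the analysed set.
2. Events count only during or after re-treatment. Further growth seen in the gap is therefore not an event either.
3. The clock nevertheless starts at first progression. The Kaplan-Meier curve stays at 1 at least until the shortest gap has passed, and each patient's time contains her own gap.

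**Size, illustration only.** Let g be the gap from first progression to first re-treatment dose and m the median time from that dose to second progression or death. Neither is in the protocol; both are assumed. With a gap common to all patients, reported time = g + time from dose, so:

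reported median = g + m, and relative increase = g / m.

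With m = 12 weeks:

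| Gap g (weeks) | Reported median (weeks) | Increase over 12 weeks |
|---|---|---|
| 1 | 1 + 12 = 13 | 1/12 = 8% |
| 4 | 4 + 12 = 16 | 4/12 = 33% |
| 8 | 8 + 12 = 20 | 8/12 = 67% |
| 16 | 16 + 12 = 28 | 16/12 = 133% |

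Over the same gaps, m = 24 weeks gives 1/24 = 4% to 16/24 = 67%, and m = 8 weeks gives 1/8 = 12% to 16/8 = 200%.

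**Unequal gaps.** A simulation assumed exponential times from first progression with a 12-week median and gaps uniform on 1 to 16 weeks, keeping only patients event-free at the end of their gap. The median was about 20.0 weeks as section 18.2.2.2 defines it and 12.0 weeks from the first re-treatment dose. Keeping the origin at first progression with delayed entry gave 12.9 weeks. That last figure conditions on surviving the shortest gap of 1 week, so a value near 1 + 12 = 13 is expected.

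**The case against.** The strongest reply is that the definition is a literal one. Sections 4.1.2 and 4.2.2 promise only the time to second progression in re-treated patients. First to second progression is a fair reading of that name, and the section openly restricts the set. Nowhere does the protocol state that the endpoint measures how long re-treatment controls disease. This stands as far as it goes: the fault lies in how the number can be read, not in a broken promise. But plain Kaplan-Meier in a set selected after the origin does not describe any group identifiable at first progression, and it does not isolate the second course.

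Re-treatment is also partly covered elsewhere. Section 18.2.2.4 reports best response, and section 18.2.2.5 reports duration of response and of disease control, over the re-treatment phase alone. The two durations cover only patients with response or disease control, so they do not replace an analysis of all re-treated patients from first dose.

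A reader might infer several stronger points that the document does not support.

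- **A guaranteed gap of at least 4 weeks.** Section 16.1.2 says progression "will be confirmed by a repeat evaluation at the next tumour assessment time point, but no sooner than 4 weeks later", but that covers unconfirmed progression before the 24-month treatment period is complete. Section 9.3.3 requires confirmation after stopping without naming an interval, and section 10.6 moves eligible, consented patients to re-treatment when they progress.
- **A gap of up to 16 weeks, from a 12-weekly scan plus 4 weeks of screening.** Section 8.1.2.1 says "All assessments must be completed within 28 days prior to the patient being re-registered". That is a look-back window, not a waiting period, and nothing stops the confirming scan from also serving as the screening scan. Nor does section 18.2.2.2 say whether diagnosis means the first or the confirmed date of progression; if the latter, the confirmation interval falls outside the clock.
- **That a later origin recovers patients lost while waiting.** It does not. The same patients are absent under either origin.
- **That the definition admits patients who progressed on initial therapy.** Under section 9.3.3 that category is empty. The conflict is one of wording and changes no patient's time.

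**Conclusion.** The concern holds in a limited form. By its own wording, section 18.2.2.2 adds guaranteed event-free time to the estimate, always upwards, relative to the time from first re-treatment dose. That needs no assumption beyond a gap longer than zero.

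The amount cannot be derived from the protocol. The medians of 13 to 28 weeks rest on an assumed 12-week median and assumed common gaps of 1 to 16 weeks, and should not be quoted as an expected bias.

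The consequences are small. The endpoint is secondary and descriptive, with no comparator or threshold. It also concerns a probably small subset, since section 9.3.3 limits re-treatment to patients who stopped in confirmed complete response or who completed 24 months without progression. The 12-of-48 rule is untouched. A statistical analysis plan might add a suitable method, but the origin and analysis set are already fixed in the protocol text.

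**What to change.** In section 18.2.2.2:

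1. Start the clock at the first dose of re-treatment. Alternatively, keep first progression as the origin and let patients enter the risk set at that dose (delayed entry). The first option is simpler; with few patients, early risk sets under delayed entry may be very small and the curve unstable.
2. Name the re-treatment screening scan, already required by section 8.1.2.1, as the reference for second progression.
3. Report the interval from first progression to first re-treatment dose as a descriptive figure, stating whether first progression is dated at first detection or at confirmation.
4. Describe the result as conditional on having started re-treatment, because patients who died or became ineligible while waiting remain outside it.
5. Reconcile the definition's reference to progression during initial therapy with section 9.3.3.

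The cost is a few sentences. No new assessments are needed, and the dates are already recorded. The one visible downside is that the reported time becomes shorter.
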